## Abstract

**Background:**

Mobile health (mHealth) interventions, using text messages to support high-school pupils to quit smoking, could be a novel and cost-effective approach. However, more research is needed, specifically to investigate long-term effectiveness. The study aims to evaluate the effectiveness of a newly developed mHealth intervention targeting smoking cessation among high-school pupils.

**Methods:**

The study is a two-arm, randomized controlled trial with an intervention group (mHealth intervention) and a control group (treatment as usual: national smoking cessation help line). Outcome measures will be investigated at baseline and at 3, 6, and 12 months’ follow-up. Primary outcome measures will be: prolonged abstinence and 4-week point prevalence of smoking abstinence. Secondary outcome measures will be: 7-day point prevalence of smoking abstinence; mean number of quit attempts since taking part in the study; number of uses of other smoking cessation services since first invitation to the study and number of cigarettes smoked weekly if still smoking.

**Discussion:**

High schools in Sweden are bound by law to offer a smoke-free environment. However, little effort has been made to offer support to pupils who wish to quit smoking; rather the emphasis is on prevention of uptake. The study will examine the effectiveness of a stand-alone mHealth intervention targeting smokers among high-school pupils.

**Trial registration:**

The trial was not retrospectively registered and has been registered at ISRCTN with the unique identification number ISRCTN15396225. The trial was registered on 13 October 2017.

**Electronic supplementary material:**

The online version of this article (10.1186/s13063-018-3028-2) contains supplementary material, which is available to authorized users.

## Background

Smoking is responsible for about 10% of the total disease burden in Sweden, and around 6000 people die every year due to smoking [1]. In Sweden, the prevalence of daily smoking among young people aged between 16 and 29 years has been stable during the last 5 years at approximately 11–13% among women and 7–10% among men. The figures for occasional smoking were approximately 19–22% for women and 22–24% for men during the same period [2, 3]. Around 25% of high-school pupils were smoking in 2016 and a third of those were daily smokers [4].

However, most tobacco control programs in schools focus on prevention of uptake rather than offering support for quitting smoking [5]. Implementation of smoking cessation interventions at the high-school level could, therefore, have a major impact on population health. A recent Cochrane review including 28 trials suggested that interventions that have shown to be effective among adults, e.g., motivational enhancement, could also be effective among adolescents. However, the review also showed that there is currently insufficient evidence to recommend a specific method of intervention for young people and that more data are needed on long-term cessation [6]. Furthermore, although recent figures show that around two thirds of high-school smokers want to quit [7], only about one in ten seeks or gains access to evidence-based interventions [8, 9].

During the last decade, the number of Internet and computerized interventions has expanded substantially, moving interventions from the health care sector to the homes of the general population. However, a meta-review, including 41 studies on online prevention aimed at lifestyle behaviors, showed that the majority of users were female, highly educated, white, and living in high-income countries. Also that the overall use of the interventions was low [10].

In contrast to Internet-based interventions delivered on computers, mobile health (mHealth) interventions have the capacity to interact in a more dynamic way as individual messages are delivered at certain predetermined intervals. Text-based interventions also offer other advantages. Users can access text-messaging services (SMS) whenever they feel an urge to smoke, and these interventions can be provided to individuals within their own environment and delivered in real time [11–14]. Also, mHealth interventions using a “push” technique, such as text messages, do not require the user to seek out information or maintain engagement by going to a website. As the growth of mobile phone ownership and usage is expected to continue to grow, mobile technology offers an innovative way to reach smokers worldwide [14].

Various challenges and tasks can be sent via text messages that require a user response. This may allow two-way communication in real-time, facilitating adherence to the intervention and providing short, timed bursts of information throughout the day. Because nearly all young people have a mobile phone, mHealth interventions could reach a large proportion of the target group and could have a significant impact as a result of the high levels of exposure, low cost, and strong adherence to text-based interventions [15, 16].

There is increasing evidence that text-messaging programs on mobile phones can help people to modify their health behaviors. The evidence is particularly strong for smoking cessation. A recent Cochrane review indicated that smoking cessation programs by text messaging increased long-term quit rates by 67% [15]. Text messages have been found to help increase access to educational and support services that promote smoking cessation across diverse populations [14]. A recent meta-review on text-message interventions for smoking cessation, including 13 studies, showed that cessation rates for the intervention group were 36% higher than for the control group [17]. An earlier review including five studies showed a similar short-term effect of text-message interventions on smoking cessation; however, limited long-term effects were found [17]. Interventions including text messages have also been found to be effective among young adults [11, 16]. A study aiming to test the efficacy of a text-based intervention in high school showed significant smoking abstinence among occasional smokers [18]. However, the study included a small sample size. A meta-analysis investigating text-messaging interventions targeting smoking among adolescents concluded that although there is supporting evidence, a greater understanding is needed on how the interventions work, i.e., mechanisms of change. Furthermore, to our knowledge, no studies have been performed in Sweden targeting high-school pupils, and there is a need for an effective intervention that can be implemented and offered via high schools.

In our previous research, we developed an mHealth intervention, NEXit, targeting smoking among university students. NEXit was developed by our research group, using formative research methods (for more details [19]). The text messages in the main NEXit study were developed based on existing evidence-based practice, expert guidance, and official smoking cessation manuals recommended in Sweden. Key elements from previous text- and Internet-based interventions were also included, e.g., problem-solving tips and distraction techniques. The effectiveness of the main NEXit intervention was evaluated in a two-arm randomized controlled trial (RCT) including 1590 participants of between 21 and 30 years of age. The trial showed a significant difference between the intervention group (25.9%) and the control group (delayed intervention) (14.6%) on 8-week prolonged abstinence. For 4-week point prevalence of complete cessation, the numbers were 20.6 and 14.2%, respectively. Students who received the intervention were almost twice as likely to quit smoking than students in the control group [20].

This article presents the study protocol of a RCT testing the effectiveness of an mHealth intervention targeting smoking among high-school pupils in Sweden.

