### Aim and hypotheses

The study aims to evaluate the effectiveness of a newly developed mHealth intervention targeting smoking among high-school pupils. The primary hypothesis is that participants in the intervention group will report significantly higher cessation rates (measured by the primary outcome measures) at follow-up compared with participants in the control group. Secondary hypotheses are that the intervention group will report significantly higher rates of 7-day point prevalence of smoking abstinence, higher mean number of quit attempts since taking part in the study, fewer number of uses of other smoking cessation services since first invitation to the study, and lower numbers of cigarettes smoked weekly if still smoking at follow-up, compared with the control group. These hypotheses are proposed at 3, 6, and 12 months’ follow-up.

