### Outcome measures

Outcome measures will be investigated via questionnaires at baseline and at 3, 6, and 12 months after enrollment. The primary outcomes will be: (1) prolonged abstinence (not smoked more than five cigarettes in the last 8 weeks) and (2) 4-week point prevalence of smoking abstinence. Secondary outcomes will be: (3) 7-day point prevalence of smoking abstinence; (4) mean number of quit attempts since taking part in the study; (5) number of uses of other smoking cessation services since first invitation to the study, e.g., calling help line; and (6) number of cigarettes smoked weekly if still smoking.

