**Fig. 2 Fig2:**
[figure not shown]
Standard Protocol Items: Recommendations for Interventional Trials (SPIRIT) Figure

School principals will be contacted via e-mail and invited to take part in the study. Recruitment will last for 6 months and be executed by paper advertising (posters and leaflets), digital advertising (e-mail, school website, or app if applicable), and by school staff (teachers, mentors, and/or school health centers). Pupils will register their interest by sending a text message to a dedicated telephone number (included in all information materials). Informed consent and the baseline questionnaire will be completed on their mobile phone. After completing the baseline questionnaire, participants will immediately be randomized to the intervention group or the control group. A text message will be sent to each participant to inform them to which group they have allocated.

All participants will be sent a follow-up questionnaire via a text message (with a link to the questionnaire) at 3, 6, and 12 months after enrollment (3-month interval will be primary outcome). Three reminders, 2 days apart, will be sent to non-responders, also via text message. In addition, participants who still do not respond will be telephoned every second day, with a maximum of three phone calls. These phone calls will only include two questions investigating the primary outcomes (prolonged abstinence and 4-week point prevalence of smoking abstinence).

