### Power calculation

The power calculation is based on our earlier research [20], where 25.9% reported prolonged abstinence in the intervention group and 14.6% in the control group, i.e., an 11.3% difference between the two groups. To achieve 80% power with a significance level of 0.05 (two-sided) and correction for continuity, a sample size of 195 persons is needed in each group. If there is 30% attrition in the follow-up measurements, the number needed in each group is 279, with a total required sample size of 558.

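### The sample size of 558 gives 80% power for prolonged abstinence only; for the second primary outcome, 4-week point prevalence, power is about 33–39% on the earlier trial's rates

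*Protocol article*

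**What the plan says.** Outcome measures in the protocol article lists the primary outcomes as "1) prolonged abstinence (not smoked more than five cigarettes in the last 8 weeks) and (2) 4-week point prevalence of smoking abstinence". Aim and hypotheses puts the primary hypothesis on both, in the plural: "participants in the intervention group will report significantly higher cessation rates (measured by the primary outcome measures) at follow-up". Participants and procedure fixes the time point ("3-month interval will be primary outcome") and limits the follow-up telephone calls to these two outcomes. Data analysis plans effect-modification analyses for both. Nowhere is one ranked above the other, and no rule says whether success needs both or either.

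The Power calculation uses one of them: "25.9% reported prolonged abstinence in the intervention group and 14.6% in the control group, i.e., an 11.3% difference between the two groups". It continues: "To achieve 80% power with a significance level of 0.05 (two-sided) and correction for continuity", and arrives at 195 per group, 279 per group after 30% attrition, and 558 as the total the trial requires. It gives no power for 4-week point prevalence. The rates for that outcome, from the same earlier trial, stand in the Background: "For 4-week point prevalence of complete cessation, the numbers were 20.6 and 14.2%, respectively".

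**The concern.** The protocol had planning rates for both primary outcomes from one source. It sized the trial on the larger difference (11.3 points) and left the smaller one (25.9 − 14.6 = 11.3 against 20.6 − 14.2 = 6.4 points) out of the calculation. A reader of the Power calculation sees one required size for a trial with two equal primary outcomes and cannot tell that one of them is much less well covered.

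What is at stake is how the 3-month result is read. If the effects match the earlier trial and attrition is as planned, the 4-week outcome is more likely than not to be non-significant (about 61% uncorrected, 67% corrected) although the effect is there. With no stated ranking, that leaves a mixed result on two co-equal outcomes and room to stress whichever one reaches significance.

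**Working it through.** **Inputs.** Prolonged abstinence 25.9% vs 14.6%; 80% power; two-sided 5%; 195 analysed per group; 30% attrition; 279 per group, 558 in total (Power calculation). 4-week point prevalence 20.6% vs 14.2% (Background). Equal allocation (Design). The main analysis uses participants with follow-up data (Data analysis), so 195 per group is the analysed number at the planned attrition.

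**Step 1: reproduce the plan's figure.** The unpooled normal formula is n = (1.960 + 0.8416)² × [p1(1 − p1) + p2(1 − p2)] / (p1 − p2)².
- Prolonged abstinence: 7.849 × (0.1919 + 0.1247) / 0.113² = 7.849 × 0.3166 / 0.01277 = 194.6, so 195. The arcsine formula also gives 195.0; the pooled formula gives 198.
- Attrition: 195 / 0.7 = 278.6, so 279 per group; 2 × 279 = 558.
- Exact binomial power at 195 per group is 80.0% without continuity correction.

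The stated 195 therefore reproduces, but only without the continuity correction that the section mentions; with it the formulas give 212 to 215. That is a separate matter. Here it only means that power should be shown both ways.

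**Step 2: power for 4-week point prevalence at 195 per group.** Difference 0.064; mean proportion 0.174.
- Standard error under no difference: √(2 × 0.174 × 0.826 / 195) = 0.03839.
- Smallest significant difference: 1.960 × 0.03839 = 0.0753, about 7.5 points. The 6.4 points of the earlier trial fall short of it.
- Standard error under the alternative: √[(0.206 × 0.794 + 0.142 × 0.858) / 195] = √(0.2854 / 195) = 0.03826.
- Power: Φ[(0.064 − 0.0753) / 0.03826] = Φ(−0.294) = 38.4%.
- With continuity correction, subtract 1/195 = 0.0051 from the difference: Φ(−0.428) = 33.4%.
- Exact binomial enumeration: 38.8% uncorrected, 33.3% corrected.

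**Step 3: the same with complete follow-up, 279 per group.** Normal approximation 51.4%, or 46.9% corrected. Exact 51.5%, or 47.0% corrected.

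**Step 4: size for 80% on this outcome.** Unpooled: 7.849 × 0.2854 / 0.064² = 546.9, so 547 per group. Pooled: 550. At 30% attrition, 547 / 0.7 gives 782 per group (1,564 in total) and 550 / 0.7 gives 786 per group (1,572 in total). With continuity correction, 581 per group, 830 randomised per group, 1,660 in total.

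| Analysed per group | Prolonged abstinence, exact power uncorrected | 4-week point prevalence, exact power uncorrected | 4-week, corrected |
|---|---|---|---|
| 195 (30% attrition) | 80.0% | 38.8% | 33.3% |
| 279 (no attrition) | 91.8% | 51.5% | 47.0% |

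**The case against.** The Power calculation hides nothing. It names the outcome it uses and never claims 80% for 4-week point prevalence, and the Background prints the smaller difference openly. Sizing on one of two primary outcomes is a common choice. This stands: what is missing is an explicit second figure, and no individual sentence is false. But the section calls 558 the size the trial requires, and the trial has two unranked primary outcomes.

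A reader might infer that the trial's power cannot exceed 39%. The documents do not support that. The figure holds at 195 analysed per group; the 30% attrition is an assumption, and the three text reminders and up to three calls are there to reduce it. Recruitment is defined as lasting 6 months, and nothing says that enrolment stops at 558. Even so, full follow-up of 558 reaches only about half.

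A reader might also infer that success needs both outcomes, so that the lower power governs the whole trial. No section states such a rule.

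The planning rates come from university students aged 21 to 30 with a delayed-intervention control, whereas this trial enrols pupils mostly aged 16 to 19 and refers controls to a help line. That makes 33–39% one scenario. The caveat applies equally to the stated 80%, which rests on the same trial. The planned covariate-adjusted logistic regression may shift power somewhat, but the documents quantify no gain, and reaching 80% would take 550 / 195 = 2.8 times the analysed sample.

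Finally, the planned odds ratios with 95% CIs will show the imprecision. They will do so only after the data are in, and they do not settle which outcome carries the conclusion.

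**Conclusion.** The point holds for the Power calculation; the Background sentence merely supplies the rates and contains no error. The 80% applies to prolonged abstinence alone. For 4-week point prevalence, which has equal primary status, power is about 33–39% at 195 analysed per group (with and without continuity correction) and about 47–52% if all 279 per group are followed up. No standard variant of the calculation at 558 randomised comes near 80%.

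This assumes the earlier trial's rates, unadjusted comparison of two proportions and a two-sided 5% level for each outcome. It does not make the trial unsound: prolonged abstinence is sized as stated if the continuity correction is set aside. It should be corrected before the trial starts, because it changes what a non-significant 4-week result can be taken to mean.

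**What to change.** Leave the sample size as it is.

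1. In the Power calculation, state that 558 is sized for prolonged abstinence only, and give the power for 4-week point prevalence under the earlier trial's rates: about 33–39% at 195 analysed per group and about 47–52% with complete follow-up.
2. Preferably, before the trial starts, name prolonged abstinence at 3 months as the single primary outcome and 4-week point prevalence as a key secondary outcome, reported with its 95% CI. Align the abstract, Aim and hypotheses, Outcome measures, Participants and procedure, Data analysis and the registry entry.
3. If both outcomes stay primary, state in advance that a non-significant 4-week result is not evidence of no effect.

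Step 1 alone repairs the omission; step 2 is a design preference that also settles which outcome carries the conclusion. The cost is wording in several sections, a registry update if step 2 is taken, and a less favourable stated power for one outcome. Trial status says that the trial had not started at submission, so the roles could still be fixed before any outcome data.

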## Methods

### Design

The study is a two-arm RCT with an intervention group (mHealth smoking cessation program) and a control group (treatment as usual: national smoking cessation help line). Equal number of individuals will be allocated in the two groups.

### Aim and hypotheses

The study aims to evaluate the effectiveness of a newly developed mHealth intervention targeting smoking among high-school pupils. The primary hypothesis is that participants in the intervention group will report significantly higher cessation rates (measured by the primary outcome measures) at follow-up compared with participants in the control group. Secondary hypotheses are that the intervention group will report significantly higher rates of 7-day point prevalence of smoking abstinence, higher mean number of quit attempts since taking part in the study, fewer number of uses of other smoking cessation services since first invitation to the study, and lower numbers of cigarettes smoked weekly if still smoking at follow-up, compared with the control group. These hypotheses are proposed at 3, 6, and 12 months’ follow-up.

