### Control group

The control group will be offered treatment as usual. High-school pupils in Sweden can turn to school-based health centers, including nurses and counselors. The school health centers do offer smoking cessation support. Participants in the control group will be informed via a text message that they have been allocated to the control group. The text message will include information on where they can gain smoking cessation support, i.e., the national smoking cessation help line offering smoking cessation support to youth. No additional prompts, reminders, or information will be given to the control group during the study.

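### The secondary outcome on use of other cessation services counts calls to the help line that is the control arm's own referral, so lower use in the intervention arm could arise without any programme effect on service seeking

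*Protocol article*

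**What the plan says.** All references are to the protocol article.

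- **Outcome.** Outcome measures defines secondary outcome 5 as "number of uses of other smoking cessation services since first invitation to the study, e.g., calling help line". Follow-up questionnaire repeats the same window and example as item 6.
- **Hypothesis.** Aim and hypotheses expects "fewer number of uses of other smoking cessation services since first invitation to the study" in the intervention group relative to control, at 3, 6 and 12 months, under an aim of evaluating effectiveness.
- **Comparator.** Design describes a "control group (treatment as usual: national smoking cessation help line" arm. Control group says of the allocation text: "The text message will include information on where they can gain smoking cessation support, i.e., the national smoking cessation help line". It adds: "No additional prompts, reminders, or information will be given to the control group during the study".
- **Intervention.** Intervention group lists the content of the 121 messages and mentions no referral to the help line.
- **Timing.** Participants and procedure places recruitment, registration, consent and baseline before allocation: "After completing the baseline questionnaire, participants will immediately be randomized to the intervention group or the control group". Quit attempts have a different window: "mean number of quit attempts since taking part in the study".
- **Analysis.** Data analysis specifies negative binomial regression with a ratio of means, tested two-sided at 5%.

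**The concern.** The outcome is labelled as use of *other* services, but its only named example is the service to which one arm is directed by design. Following the allocated referral therefore adds to the control count, and a higher control count is what the secondary hypothesis predicts. Two mechanisms can produce the same ratio:

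1. Referral uptake: controls call the help line because a text told them where to find it.
2. Substitution: pupils receiving the programme seek less support elsewhere.

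Only the second says anything about what the programme does to service seeking. If the follow-up item records one number, the analysis cannot tell them apart afterwards. At stake is the interpretation of one secondary outcome; neither primary outcome uses this item.

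There is also a separate, smaller weakness. The count runs from first invitation, so it includes use that allocation cannot have influenced. For a pupil reached by a poster, a leaflet or a member of staff, first invitation is not a clearly dated event.

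**Working it through.** The article states no expected rate or target ratio for this outcome, so there is no figure to reproduce. The check sets the sections side by side and then illustrates the possible size.

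**Step 1. Is the help line both comparator and outcome?** Yes. Design and Control group name it as what controls are referred to. Outcome measures and Follow-up questionnaire name calling the help line as an instance of the counted event. No section separates help-line calls from other services.

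**Step 2. Illustration of size.** Only two inputs come from the article: 195 per arm (Power calculation, the number after 30% attrition; 279 × 0.70 = 195.3) and the two-sided 5% level. The mean counts and the dispersion are assumptions.

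- n = 195 per arm; dispersion k = 1 (assumed).
- m_I = mean uses in the intervention arm = 0.2 (assumed).
- m_C = 0.2 + r, where r is the extra help-line calls per control prompted by the referral (assumed 0.05, 0.10, 0.20). The programme has no effect.
- Ratio of means = m_I / m_C.
- SE of the log ratio = √[(1/m_I + k)/n + (1/m_C + k)/n].
- Chance of a significant lower-use result = Φ[ln(m_C/m_I)/SE − 1.96].

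Worked for r = 0.10: SE = √[(5 + 1)/195 + (3.333 + 1)/195] = √0.0530 = 0.230. ln(0.3/0.2) = 0.405. 0.405/0.230 − 1.96 ≈ −0.20, so the chance is about 42%.

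| Extra calls per control, r | Ratio, base 0.2 | Chance | Ratio, base 0.4 | Chance |
|---|---|---|---|---|
| 0 | 1.00 | 2.5% | 1.00 | 2.5% |
| 0.05 | 0.80 | 15% | 0.89 | 9% |
| 0.10 | 0.67 | 42% | 0.80 | 23% |
| 0.20 | 0.50 | 88% | 0.67 | 63% |

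The telephone follow-up asks only the two primary-outcome questions, so fewer than 195 per arm may answer this item. The chances would then be lower; the ratios would not change.

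**Step 3. What does the early window do?** Use before randomisation has the same expected value in both arms. Add an assumed 0.1 such uses to each arm, with base 0.2:

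| r | Ratio, post-randomisation only | Ratio with early window | Chance, post-randomisation only | Chance with early window |
|---|---|---|---|---|
| 0 | 1.00 | 1.00 | 2.5% | 2.5% |
| 0.05 | 0.80 | 0.86 | 15% | 11% |
| 0.10 | 0.67 | 0.75 | 42% | 30% |
| 0.20 | 0.50 | 0.60 | 88% | 75% |

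With no referral effect (r = 0) the ratio stays at 1.00. The early window pulls the ratio towards 1, against the hypothesised direction.

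**The case against.** **The comparison is honest as worded.** The trial compares the programme with treatment as usual, which the article says is the help line. The hypothesis is only that one group reports fewer uses than the other, and a ratio below 1 supports exactly that. The article does not call fewer uses a benefit. A 12-week programme may also displace other support, which would be a real effect of allocation. This stands against a stronger reading that a reader might take: that a significant ratio would show nothing but the referral, or could not support the hypothesis. The documents do not go that far. What remains is that the ratio mixes two mechanisms and sits under an effectiveness aim.

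**The referral is weak.** It is one text without reminders, and nothing stops intervention pupils from calling the help line. Some controls may not regard the help line as an *other* service and so leave it out. All this stands. It means the size is unknown and could be small, and that the item may mean different things in the two arms.

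**Usual care is wider than the help line.** Control group also mentions school health centres, so taking out help-line calls would not remove all usual care from the count. True, but those centres are described as available to pupils generally, whereas the help line is what the allocation text specifies. This favours reporting both components over discarding one.

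**The analysis plan may deal with it.** It is not shown and could add detail. However, the article itself fixes the definition, the window and the direction, and describes one count. An analysis plan cannot split a count that the questionnaire did not collect separately.

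**Conclusion.** The point holds as a limit on interpretation. The help line is the control arm's referral and also the named example of the counted event, so the hypothesised lower use in the intervention arm could appear without any programme effect on service seeking. A single combined count cannot resolve which mechanism is at work.

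The size cannot be taken from the article. The illustrated ratios of 0.80, 0.67 and 0.50, with chances of about 15%, 42% and 88%, rest on an assumed base of 0.2 uses per pupil, dispersion 1, 195 per arm and assumed referral effects. With a base of 0.4 the chances fall to about 9%, 23% and 63%. The Background's statement that about one in ten young smokers seeks or gains access to evidence-based help does not supply the base rate: it is a proportion of people with no stated period, not a mean count over this window.

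A reader might also infer that counting from first invitation helps to build in the difference. It does not. Use before randomisation is balanced in expectation, adds noise and dilutes the contrast. It is a separate weakness of the window.

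This concerns one of four secondary outcomes. The primary outcomes, the sample size and the primary conclusion are unaffected.

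**What to change.** 1. Count uses since randomisation. Allocation follows directly on the baseline questionnaire, so this gives pupils a definite starting point and brings the window into line with the one already used for quit attempts.
2. Split the follow-up item in two: contacts with the national help line, and uses of any other cessation service.
3. Report help-line contact by arm as uptake of the comparator referral.
4. Reword the secondary hypothesis, and state in advance that a difference in total use will be read as use of the assigned referral plus co-intervention, not as evidence of programme effectiveness.

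The cost is one slightly longer follow-up question and a reworded secondary hypothesis. According to Trial status, the trial had not started at submission, so the questionnaire could still be changed at that point without losing data.
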